## ***Trials* structured Study Protocol template**

*Trials* guidance: the numbers in curly brackets (e.g. {5a}) are SPIRIT item identifiers. **Please do not remove the numbers in curly brackets, or any heading that contains them.** The item identifiers are slightly out of sequence to make the document flow more easily but it is important that they remain in the document to allow electronic searches by SPIRIT item number.

If you are certain that an item does not apply, please state "n/a" and provide a short explanation. Leaving an item blank or stating "n/a" without an explanation will lead to your manuscript being returned before review.

NB: All text in green can be removed once you have finished creating your Study Protocol. Text in black is mandatory. Please also read the submission guidelines for Study Protocols prior to submitting to *Trials*: <https://trialsjournal.biomedcentral.com/submission-guidelines/preparing-your-manuscript/study-protocol>

### **Abstract**

- **Background:** Inadequate and/or poor quality sleep in early childhood impairs social-emotional and cognitive function (via effects on the developing brain), and markedly increases obesity risk (via hormonal and endocrine effects). Short sleep duration, behavioral sleep problems and sleep-disordered breathing peak at 20%-50%, during the preschool years (ages 3-5). Healthy sleep habits increase sleep duration and prevent behavioral sleep problems. Awareness of sleep-disordered breathing symptoms leads to timely treatment for it. Despite ample data on sleep problems "...much less work has been done on effective strategies to promote sleep as a healthy behavior (CDC 2013)". This study's overarching goal is to empower families of preschool children with the knowledge and skills needed for healthy sleep, and to recognize a sleep problem. It builds on work in Head Start, an early childhood education (ECE) program for disadvantaged preschool children and their families: The team's Early Childhood Sleep Education Program (ECSEP™) educates Head Start teachers, children, and parents about healthy sleep in a way they can process and understand. In a randomized controlled trial, the children in the ECSEP group slept 30 minutes longer/night.
- **Methods:** The proposed study will implement a Social-Ecological web of multi-level interventions to reinforce the ECSEP, and to promote healthy sleep throughout ECE. Within Head Start, the team will create new delivery platforms (print & video, family

visits) that 'amplify' the ECSEP. Beyond Head Start, the team will educate communities, and partner with stakeholders on strategies designed to embed 'sleep health literacy' in ECE policy. This project will: 1) Adapt sleep education material into additional multi-media formats, and; apply the Health Care Institute model to train Head Start staff to mount interventions and collect data. 2) Enroll 540 parent-child dyads from 7 Head Start agencies in New York in a stepped wedge randomized controlled trial.

Investigators will analyze trial effects on primary outcomes: a) child sleep duration, b) parent knowledge, attitudes, self-efficacy and behavior, and c) child sleep difficulties.

3) Assess the feasibility of screening and guidance for sleep problems (vs. sleep health) for a future efficacy study. Secondary outcomes are: classroom behaviors, policy change, and process data.

- **Discussion:** Poor sleep in early development has ramifications for years to come, perhaps through adulthood. Head Start serves low-income, mainly racial-ethnic minority families, in whom sleep health disparities are greatest-- but are modifiable.

**Trial registration:** [NCT03556462](https://www.clinicaltrials.gov/ct2/show/study?term=NCT03556462&rank=1)

## Keywords

*Trials guidance:* sleep health, children, sleep, Head Start

## Introduction

### Background and rationale {6a}

Young children need sufficient, healthy sleep for optimal cognitive, social-emotional, and physical development, and to reduce obesity risk. At preschool-age (3-5 years), 10-13 hours of sleep per day inclusive of naps, is recommended. Yet, prior to school-entry up to one-third of US children don't sleep this much. Additionally, 25-30% of preschoolers experience difficulties falling and staying asleep, i.e., behavioral sleep problems (BSPs). Yet, optimal sleep hygiene practices at this age— a consistent bedtime and bedtime routine, falling asleep on one's own, limiting screen time before bed, etc.— are associated with fewer BSPs and longer sleep duration. Parent knowledge and attitudes about child sleep are significantly associated with the quality and quantity of young children's sleep. Generally, improved sleep hygiene and parent education are associated with positive effects on children's sleep and household routine, and no risks.

### Objectives {7}

This was a primary prevention trial of sleep health interventions in Head Start. This RCT of multi-level interventions grounded in the social-ecological model examined the following outcomes at ~9- and 12-month follow-up: a) child sleep duration, b) child sleep difficulties, and c) parent knowledge, attitudes, beliefs, and self-efficacy (KASB) regarding children's sleep.

-SLEEP DURATION (CHILD): Hypothesized differences in sleep duration for Intervention vs. Control periods were: a) longer duration for Intervention periods (Primary Outcome: difference at FU3 [app. 9 month follow-up]), b) >30-minute difference at FU3, and c) a 15-minute difference in duration at FU4 (app. 12 months). Sleep duration was measured via parent-reported sleep logs.

-SLEEP DIFFICULTIES (CHILD): Hypothesized differences between Intervention vs. Control periods were: a) lower mean total scores, b) lower odds of scores  $\geq 8/36$  and c) fewer parents reporting a sleep problem in the 10th Tayside item (Yes/No). Surveys with at least 7 of 9 items scored were included in analysis. The Tayside Children's Sleep Habits Questionnaire was used to assess this outcome. (Secondary outcome)

-KNOWLEDGE-ATTITUDES-SELF EFFICACY- BELIEFS (PARENT): Hypothesized differences in parents'

KASB for Intervention vs. Control periods were: a) higher KASB total scores and b) higher scores for each domain. KASB scales with at least 80% non-missing responses were included in analysis. The KASB survey was developed to align with the main educational intervention, the Early Childhood Sleep Education Program. (Secondary outcome)

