## **Trial design {8}**

Stepped Wedge Cluster Randomized Controlled Trial. The 7 agencies were randomized: 4 agencies (and 12 sites that operate under them) and 3 agencies (and 11 sites that operate under them) were randomized to Wedge 1 and Wedge 2, respectively.

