## Outcomes {12}

Outcomes were parent-reported school-night sleep duration per sleep logs (primary: at 9 months; secondary: at 12 months), mild/moderate sleep difficulties per validated questionnaire, and KASB total and domain scores at 9 and 12 months (secondary)

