## Participant timeline {13}

|         |                 |                                     |                                    | Control                             | Intervention                       |                       |
|---------|-----------------|-------------------------------------|------------------------------------|-------------------------------------|------------------------------------|-----------------------|
| Wedge 1 | April-Sept KASB | Sept 2018                           | Nov 2018                           | Jan 2019                            | Mar 2019                           | Sept 2019             |
|         | Baseline        | Baseline                            | Follow-Up Data 1                   | Follow-Up Data 2                    | Follow-Up Data 3                   | Follow-Up Data 4      |
|         |                 | 1-week before Wedge 1 Interventions | 1-week after Wedge 1 Interventions | 1-week before Wedge 2 Interventions | 1-week after Wedge 2 Interventions | 1 Year after Baseline |
|         | KASB TAYSIDE    | Log                                 | Log KASB TAYSIDE                   | Log                                 | Log KASB TAYSIDE                   | Log KASB TAYSIDE      |
|         | KASB TAYSIDE    | Log                                 | Log KASB TAYSIDE                   | Log                                 | Log KASB TAYSIDE                   | Log KASB TAYSIDE      |

Figure 2

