## Sample size {14}

Mean school night sleep duration at **FU3 (app. 9 months)** was the primary outcome. Clinically significant effects are evident from an additional 30-35 minutes of nighttime sleep. With 7 agencies, a sample of n=173 provides 90% power to detect a difference as small as 15 minutes between Intervention vs. Control phases ( $p < .05$ , 2-tail). For parent KASB, a secondary outcome, a sample of n=450 provides >97% power to detect a moderate effect size (Cohen's  $d = 0.3$ ) for each of its named scales.

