## Assignment of interventions: allocation

### Sequence generation {16a}

Randomization was at the agency level. The 7 agencies were randomly assigned by a computer to implement interventions in Fall 2018 (Wedge 1) or Spring 2019 (Wedge 2)

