## **Statistical methods**

### **Statistical methods for primary and secondary outcomes {20a}**

#### **STATISTICAL ANALYSIS PLAN**

Summary statistics of continuous variables were calculated as means and standard deviations; frequency distributions (n and %) are shown for discrete variables. To analyze treatment effect we fitted multi-level generalized linear models with the study outcome variables as dependent variables, an indicator for post-intervention status, indicators for the study phase (follow-ups 1 through 4, baseline as reference category), and covariates to adjust for age, child sex, Hispanic ethnicity, and race. Random intercepts at the agency and participant levels were included. For continuous outcomes (sleep duration, questionnaire scale scores) the identity link and gaussian error family were used. The coefficient of the post-intervention indicator is the estimate of the average treatment effect and is presented along with its 95% confidence interval (CI). For the dichotomous outcomes (positive Tayside questionnaire, parent-reported sleep problem), the log link and logistic error family were used. In this model the treatment is the odds ratio (exponentiated coefficient) of the post-intervention indicator, presented with its 95% CI.

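### The FU3 primary difference and the FU4 hypothesis have no concurrent control; the SAP's single pooled coefficient stands in for them only under an unstated constant-effect assumption that the hypotheses contradict

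*Combined protocol and SAP*

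**What the plan says.** Objectives {7} frames the sleep-duration hypotheses as Intervention against Control periods. Hypothesis a), the primary one, is "longer duration for Intervention periods (Primary Outcome: difference at FU3 [app. 9 month follow-up". Hypothesis b) expects more than 30 minutes at FU3, and hypothesis c) expects "a 15-minute difference in duration at FU4 (app. 12 months". Outcomes {12} gives the time points for sleep duration as "primary: at 9 months; secondary: at 12 months", and Sample size {14} repeats that "Mean school night sleep duration at FU3 (app. 9 months) was the primary outcome".

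On the design, Trial design {8} says that 4 and 3 of the 7 agencies "were randomized to Wedge 1 and Wedge 2, respectively". Sequence generation {16a} says they were "randomly assigned by a computer to implement interventions in Fall 2018 (Wedge 1) or Spring 2019 (Wedge 2". Participant timeline {13} places FU3 (Mar 2019) "1-week after Wedge 2 Interventions" and FU4 in Sept 2019.

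On the analysis, Statistical methods {20a} fits a multi-level model with "an indicator for post-intervention status, indicators for the study phase (follow-ups 1 through 4, baseline as reference category", plus covariates and random intercepts for agency and participant. The coefficient of the post-intervention indicator is taken as the average treatment effect. The model has no term that lets the effect differ by visit or by time since intervention.

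**The concern.** A difference between Intervention and Control at a named visit needs some agencies still in control at that visit, or an assumption that carries the effect over from visits where some were. On the protocol's own calendar nobody is in control at FU3 or FU4, and the SAP states no such assumption.

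At stake is how the main result is described. An estimate whose information on treatment comes from FU1 and FU2 (Nov 2018 and Jan 2019) could be reported as a randomised effect at 9 or 12 months. If the effect fades or grows with time, that label would misstate its size at those visits. The same applies to the secondary outcomes (the Tayside questionnaire and KASB) at 9 and 12 months.

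**Working it through.** **1. The plan's own figure.** Sample size {14} claims 90% power for 15 minutes with n=173, two-sided 5%. It gives no SD, ICC or within-child correlation, so the claim cannot be reproduced. Back-solving, SD = 15/[(1.960+1.282)·√(4/173)] = 30.4 min if 173 is the total in two equal groups. With √(1/173) for a paired comparison, the SD of the difference is 60.9 min. The statement concerns Intervention and Control phases rather than a contrast at FU3. Nothing below depends on it.

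**2. Exposure by visit**, from Trial design {8}, Participant timeline {13} and Sequence generation {16a}. The log schedule in {18a} agrees: logs bracket each wedge's intervention, and a last one follows at one year.

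| | Baseline (Sept 2018) | FU1 (Nov) | FU2 (Jan 2019) | FU3 (Mar) | FU4 (Sept) |
|---|---|---|---|---|---|
| Wedge 1 (4 agencies) | 0 | 1 | 1 | 1 | 1 |
| Wedge 2 (3 agencies) | 0 | 0 | 0 | 1 | 1 |
| Treated | 0/7 | 4/7 | 4/7 | 7/7 | 7/7 |

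**3. Are visit-specific effects estimable?** Take 5 period effects and 4 treatment effects, one for each of FU1 to FU4: 9 columns. At FU3 and FU4 the treatment column equals the period column, so the rank is 7. Effects at FU1 and FU2 are estimable; those at FU3 and FU4 are not.

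**4. What the SAP coefficient uses.** With free period effects, treatment information comes only from the Wedge 1 minus Wedge 2 differences d0 to d4 (baseline to FU4). The exposure difference is x = (0,1,1,0,0). Agency and participant random intercepts give the d's a compound-symmetric covariance, proportional to aI + bJ, where J is the matrix of ones. For ICC ρ, within-child correlation r (within agency) and m children per agency:

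- b = ρ + (1−ρ)r/m and a = (1−ρ)(1−r)/m
- estimate = 0.5(d1 + d2) − w(d0 + d3 + d4), with w = b/(a + 3b)

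ρ and r are not in the documents, so I assume ρ from 0 to 0.10 and r from 0.3 to 0.7. I also assume equal agency sizes and complete data. m is 173/7 = 24.7 (Sample size {14}) or 540/7 ≈ 77 (the enrolment target in the Abstract).

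- Low end (ρ=0, r=0.3; m cancels): w = 0.3/(0.7+0.9) = 0.19.
- Middle (ρ=0.03, r=0.5, m=24.7): b = 0.0496, a = 0.0196, w = 0.0496/0.1685 = 0.295.
- High end (ρ=0.10, r=0.7, m=77): b = 0.1082, a = 0.0035, w = 0.1082/0.3281 = 0.33.

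The weight is +0.50 at FU1 and at FU2 in every case. FU3 and FU4 enter only as a subtracted comparison of two treated wedges, so any effect common to both wedges there cancels.

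**5. Illustrations with assumed effects in minutes, w = 0.295.**

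- Constant 30 throughout: 0.5(30+30) − 0 = 30.0, which is correct at every visit.
- Zero at FU1 and FU2, then 30 for everyone at FU3 and FU4: estimate 0.0.
- 20 at FU1 and FU2, then none: estimate 20.0; true effect 0 at FU3 and FU4.
- Fading (Wedge 1: 30, 20, 15, 10; Wedge 2: 30, 15): 0.5(50) − 0.295[(15−30)+(10−15)] = 25 + 5.9 = 30.9. The true mean is (4·15+3·30)/7 = 21.4 at FU3 and (4·10+3·15)/7 = 12.1 at FU4.
- Growing (Wedge 1: 10, 20, 30, 40; Wedge 2: 10, 25): 15 − 0.295·35 = 4.7. The true means are 21.4 and 33.6.

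**6. Tayside and KASB.** The timeline has no FU2 assessment for either, so FU1 is their only visit with concurrent control.

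**7. Labels.** The Sept 2018 log to Mar 2019 is 6 months, and Mar to Sept 2019 is another 6. The labels 9 and 12 imply a gap of 3 months. At FU3, Wedge 2 is one week past its intervention and Wedge 1 about four months past its FU1.

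**The case against.** The best defence is that the wording about periods and phases, read with the SAP, points to the usual stepped-wedge contrast pooled over all visits. On that reading the trial does have controls: all agencies at baseline and three at each of FU1 and FU2. If the effect is the same at every period and time since intervention, the pooled coefficient is valid and applies at FU3 too, as the constant-30 case shows. This stands. A reader might infer that the primary hypothesis cannot be estimated at all, or that the plan rests on a plain before-after comparison. The documents support neither: hypothesis a) is estimable under the constant-effect assumption, and the phase indicators adjust for calendar period. Nor is a bare Wedge 1 versus Wedge 2 comparison at FU3 planned anywhere.

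The defence does not rescue hypotheses b) and c). One coefficient cannot exceed 30 minutes and also be 15, and expecting a smaller effect at FU4 contradicts the constancy that the pooled reading needs. A model in time since intervention could estimate such effects (full rank, 9 of 9 columns), but only if they are the same in both wedges, and the SAP contains no such model.

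A reader might also infer that FU3 is simply mislabelled and belongs at 6 months. That goes too far. The timeline has an April to September baseline column, recruitment ran from March to September 2018, and Wedge 2 is dated Winter/Spring in one section and Spring in another. The origin is unclear. What stands is a conflict between dates and labels.

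**Conclusion.** The point holds as a mismatch between the stated estimand on one side and the design and SAP on the other. At FU3 and FU4, 0 of 7 agencies are in control, and visit-specific effects there are fully confounded with period. This follows from the schedule alone, given that Wedge 1 does not return to control. The comparator section calls the design a cross-over, but nothing describes a return, and the post-intervention indicator implies none.

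The pooled coefficient is a legitimate estimate, driven by the +0.50 weights at FU1 and FU2. Those weights and the negative signs elsewhere hold in every case examined. The size of the negative weights (about -0.19 to -0.33) depends on the assumed ICC, within-child correlation and agency size. The effect patterns in the illustrations are also assumed: they show how far the coefficient could depart from the FU3 or FU4 effect, not that it did. The stated 90% power is neither confirmed nor refuted.

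**What to change.** - Define the primary estimand as the pooled Intervention-versus-Control effect from the SAP model, and state that it assumes an effect constant over period and time since intervention.
- State that the randomised information on treatment comes from the FU1 and FU2 contrasts, and report both relative to baseline.
- Withdraw the FU3- and FU4-specific differences, including hypotheses b) and c), as controlled comparisons. Report those visits as uncontrolled follow-up, or from a time-since-intervention sensitivity model that states its assumption of equal exposure-time effects in both wedges.
- Apply the same to Tayside and KASB, naming FU1 as their only concurrent contrast.
- Reconcile the 9- and 12-month labels with the timeline dates, and state the time origin.
- Disclose all of this as decided after data collection, since the protocol says the trial is complete.

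The cost is rewording in Objectives, Outcomes, Sample size and the SAP, plus one optional sensitivity model. No new data are needed. The downside is that the controlled claim covers a shorter follow-up and the redefinition is post hoc.

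### The sleep-duration hypotheses are set at FU3 and FU4, but the model gives one pooled effect, no FU3- or FU4-specific effect can be estimated, and the >30-minute claim has no criterion

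*Combined protocol and SAP*

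**What the plan says.** Objectives {7} lists three hypotheses for child sleep duration: "a) longer duration for Intervention periods (Primary Outcome: difference at FU3", then "b) >30-minute difference at FU3", then "c) a 15-minute difference in duration at FU4 (app. 12 months". Outcomes {12} and Sample size {14} likewise place the primary outcome at about 9 months (FU3).

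The statistical analysis plan in {20a} fits one multilevel model per outcome, with a post-intervention indicator, indicators for follow-ups 1 to 4, covariates, and random intercepts for agency and participant. It states: "The coefficient of the post-intervention indicator is the estimate of the average treatment effect", to be shown with its 95% CI. There is no intervention-by-phase term, no null value of 30, no confidence-limit rule, and no order among the three hypotheses. The section on additional analyses {20b} adds nothing on this.

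Sample size {14} claims "90% power to detect a difference as small as 15 minutes" at a two-sided 5% level and cites 30 to 35 extra minutes as clinically significant. The Abstract says of the team's previous randomized trial that "the children in the ECSEP group slept 30 minutes longer/night".

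Trial design {8} puts 4 agencies in Wedge 1 and 3 in Wedge 2. The Participant timeline {13} places FU1 just after the Wedge 1 interventions, FU2 just before those of Wedge 2, FU3 just after those of Wedge 2, and FU4 a year after baseline.

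**The concern.** The hypotheses are about particular follow-ups, and the estimate is not. A pooled coefficient would be reported as the 9-month result for (a) and (b), and perhaps as the 12-month result for (c), although the randomized comparison behind it comes from earlier phases.

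The plan's own hypotheses also expect the effect to differ over time: more than 30 minutes at FU3 and 15 at FU4. The model assumes one constant effect, under which (b) and (c) cannot both be true.

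Hypothesis (b) has a second gap. Thirty minutes is the lower end of the range that the plan calls clinically significant, yet nothing says what result would support exceeding it. The standard could therefore be chosen after the results are seen.

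**Working it through.** **1. Can an FU3 or FU4 effect be estimated?** Exposure by period, inferred from {8} and {13}:

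| | Baseline | FU1 | FU2 | FU3 | FU4 |
|---|---|---|---|---|---|
| Wedge 1 (4 agencies) | 0 | 1 | 1 | 1 | 1 |
| Wedge 2 (3 agencies) | 0 | 0 | 0 | 1 | 1 |

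The {20a} model has an intercept, four phase terms and one post-intervention term. Its design matrix has rank 6 of 6, so the pooled effect is estimable. An added FU3-specific effect has a column equal to 1 for every agency at FU3, which is the FU3 phase indicator itself, and the rank stays at 6 of 7. Adding an FU4-specific effect as well leaves it at 6 of 8. This needs no assumed SD or ICC.

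**2. Where does the pooled estimate come from?** Let D be the Wedge 1 minus Wedge 2 difference in mean sleep duration at a period. Take a simplified model with equal-sized agencies and one exchangeable correlation. The pooled estimate is then

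0.5 × (D at FU1 + D at FU2) − w × (D at baseline + D at FU3 + D at FU4),

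with w = 0 at correlation 0, 0.19 at 0.3 and 0.32 at 0.9. FU3 and FU4 enter only as reference periods in which both wedges have the same exposure status. The treatment contrast is that at FU1 and FU2.

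**3. The plan's own figure.** {14} says "a sample of n=173 provides 90% power to detect a difference as small as 15 minutes". No SD, ICC or within-child correlation is given, so 173 can be neither reproduced nor refuted. The implied standard error is

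SE = 15 / (1.960 + 1.282) = 4.63 minutes.

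This corresponds to an SD of 30.4 minutes if 173 is the total of two independent groups, 43.0 if it is the number per phase, or an SD of within-child differences of 60.9 if the comparison is paired. With two independent groups, an assumed SD of 25, 30, 35 or 40 gives a total of 118, 170, 230 or 300.

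**4. What would support >30 minutes?** Require the lower 95% limit of the pooled effect to exceed 30.

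- At SE 4.63, the estimate needed is 30 + 1.96 × 4.63 = 39.1 minutes.
- An estimate differs from zero once it passes 1.96 × 4.63 = 9.1 minutes. Anything from 9.1 to 39.1 excludes zero without excluding 30.
- If all 540 dyads counted and the SE scaled with 1/√n, then SE = 4.63 × √(173/540) = 2.62 and the estimate needed is 30 + 1.96 × 2.62 = 35.1 minutes.
- With a t reference on 5 degrees of freedom (assumption, for 7 agencies) and SE 4.63, the estimate needed is 30 + 2.571 × 4.63 = 41.9 minutes.

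Power = Φ((true − 30)/SE − 1.96) for the normal rows, and the non-central t for the last:

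| True effect (min) | 30 | 35 | 40 | 45 |
|---|---|---|---|---|
| SE 4.63 | 2.5% | 19% | 58% | 90% |
| SE 2.62 (540 dyads) | 2.5% | 48% | 97% | >99% |
| SE 4.63, t on 5 df | 2.5% | 14% | 42% | 74% |

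**The case against.** Several points on the other side are sound. The plan attaches the primary label to (a) alone. {14} already presents 30 to 35 minutes as a clinical benchmark, and (b) stands in a list of hypothesized differences, so it can be read as an expected size. The 95% CI will be published, so a reader can see whether 30 is excluded for the average effect. The trial is complete ({23}), so any rule added now is post hoc. These points limit the remedy to wording and labelling. They do not supply an FU3 or FU4 estimate.

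It may also be said that under a constant effect the pooled coefficient is the FU3 effect. That is true under that assumption, but the plan does not state it, and (b) and (c) together contradict it.

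Three stronger readings are tempting and are not supported:

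- A reader might infer that only (b) and (c) lack a matching analysis and that (a) is sound. But (a) is also defined at FU3, so the same gap applies.
- A reader might infer that the plan would take significance against zero, or an estimate above 30, as confirming (b). {20a} promises only an estimate with a CI. The null of zero is inferred from {14}, and no section says what would confirm (b).
- A reader might infer that the trial is too imprecise to show more than 30 minutes. That depends on a back-calculated SE and on the true effect: at SE 4.63, a true 45 would be confirmed with 90% power. The 2.5% at a true 30 is the error rate of the rule in any design. The 50% chance that the estimate exceeds a true 30 holds for any symmetric, unbiased estimator. At SE 4.63 that chance falls to 14% at a true 25, 1.5% at 20 and 0.06% at 15.

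**Conclusion.** The point holds as a mismatch between hypotheses and estimand. All three sleep-duration hypotheses are stated at follow-ups where every agency has been treated, and the planned model cannot produce an effect specific to either one. What it can produce is a pooled Intervention-versus-Control effect, driven by the FU1 and FU2 contrast between wedges. This conclusion rests only on the timeline and the model terms. Hypothesis (b) additionally lacks a criterion.

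The numerical part is context and is conditional. Within the 30 to 35 minutes that the documents themselves cite, a lower-limit criterion would more often fail than succeed: power at a true 35 is 19% at the implied SE and about 48% under the optimistic 540-dyad scaling. The assumptions are the back-calculated SE, normal theory, and, for the second figure, an SE that shrinks with the number of dyads despite only 7 agencies.

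The primary comparison remains estimable as a pooled effect. What is unprotected is its description as a 9-month result and any claim of more than 30 minutes.

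**What to change.** In Objectives {7} and Statistical methods {20a}, with Outcomes {12} and Sample size {14} brought into line:

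1. State that the confirmatory contrast for (a) is the pooled Intervention-versus-Control effect from the {20a} model, and that it is not specific to FU3.
2. Relabel the 30 minutes in (b) as a clinical benchmark. Say that the pooled effect exceeds it only if its lower 95% confidence limit is above 30.
3. Report FU3 and FU4 differences, including (c), as descriptive changes without a concurrent control.
4. Mark all three changes as post hoc, because the trial is complete and agency results have already been sent out ({31a}).

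The cost is a few sentences and no new data. The downside is that the >30-minute claim will probably not be confirmed if the true effect lies in the 30 to 35 minute range, and that the 9- and 12-month claims become descriptive.
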